**Fig 2 pone.0326861.g002:**
[figure not shown]
Overview of the High-Intensity Interval Exercise Protocol. Notes: PPO, peak power output.

After a 5-minute recovery (for photoplethysmography re-instrumentation), assessments will proceed within the peak ANS-CV modulation window (10–30 min post-exercise) [65]. The order prioritizes transient ANS-CV effects first, followed by cerebrovascular and cognitive assessments (after 41 min total), as exercise-induced cognitive benefits persist longer than cardiovascular effects [66]. Alternate forms of the CVLT-III, SDMT, and COWAT will be used for post-HIIE assessments to avoid familiarization effects. Fig 3 outlines the planned testing procedures for V2 (Fig 3).

**Fig 3 pone.0326861.g003:**
[figure not shown]
Study Procedures for the Experimental Visit. Notes: BP, blood pressure; COWAT, Controlled Oral Word Association Test; CVLT-III, California Verbal Learning Test Third Edition; FCT, face-cooling test; HIIE, high-intensity interval exercise; HR, heart rate; MCAv, middle cerebral artery blood flow velocity; PCAv, posterior cerebral artery blood flow velocity; RPE, rating of perceived exertion; SDMT, Symbol Digit Modalities Test; SUT, sit-up test.

### Measurements and tests

#### Physical activity and psychological distress questionnaire.

Physical activity will be assessed using the International Physical Activity Questionnaire-Short Form (IPAQ-SF) developed for the non-injured control group and the Leisure Time Physical Activity Questionnaire, which was developed specifically for People with SCI (LTPAQ-SCI) for the SCI group. The IPAQ-SF evaluates physical activity over the past 7 days, capturing vigorous, moderate, and walking intensities, as well as sedentary behavior, providing a comprehensive activity profile [67]. The LTPAQ-SCI is an SCI-specific tool measuring mild, moderate, and heavy intensity leisure-time physical activity over the same period, with a structure similar to the IPAQ-SF [68,69]. Both self-administered questionnaires are validated, widely used, and take less than 5 minutes to complete [67–69]. Psychological distress will be evaluated using Hospital Anxiety and Depression Scale (HADS) designed to identify symptoms of anxiety and depression in both the general population and individuals with SCI [70–72]. The HADS consists of 14 items, evenly divided into two subscales: anxiety (HADS-A) and depression (HADS-D). Each subscale contains 7 items, with participants rating their experiences over the past week on a 4-point Likert scale. This tool provides a reliable and efficient evaluation of psychological distress, making it suitable for use in clinical and research settings [70–72].

#### Cardiovascular function.

**Sit-up test (SUT)***:* The SUT will be conducted using a wheelchair equipped with a reclining function down to 0 degrees (supine). Participants will initially be positioned in the reclined wheelchair for 15 minutes. Subsequently, they will be gently assisted into a seated position, with their feet placed on the floor, and asked to maintain this posture for another 15 minutes. During this seated phase, participants will be monitored for BP and HR, and questioned for symptoms of orthostatic hypotension, such as blurry vision, dizziness, light-headedness, or nausea. HRV and SBPV will also be obtained afterwards through the original BP and HR data. The SUT is recognized as a reliable method to induce an orthostatic challenge in individuals with SCI [62].

**Face-cooling test (FCT)**: A pliable plastic bag filled with 2.5 L of ice water (~0°C) will be placed on participants’ forehead, the bridge of the nose, and cheeks for 1 min. A duration of one-minute FCT activates the trigeminal nerve, leading to a transient surge in cardiovascular parasympathetic activity and bradycardia [73]. During the FCT, BP, HR, HRV, and SBPV will be assessed to monitor these cardiovascular responses.

#### Cerebrovascular function.

Cerebrovascular function will be assessed using CBFV during cognitive testing (see the Cognitive Function section below). In order to ensure that hemispheric differences in velocity does not inﬂuence the results, which do occur in the MCA and PCA [74], CBFV will be consistently recorded in the right MCA and the left PCA (P1 segment) during cognitive testing.

#### Cognitive function.

**North American Adult Reading Test (NAART)**: The NAART consists of a list of 61 words printed in order of increasing difficulty. The words are relatively short to avoid the possible adverse effects of reading stimulus complexity, and they are all ‘irregular’ with respect to the common rules of pronunciation to minimize the possibility of reading by phonemic decoding rather than word recognition. The subject would read aloud down the list of words and the number of errors made is recorded. Premorbid intelligence can be predicted by the NAART score [53].

**Stroop test**: The Stroop Test consists of three sections including: (1) Word Reading (WR), where subjects will be required to read three words (red, green, blue), printed in black ink, in a randomized and repeated manner as quickly as possible; (2) Color Naming (CN), involving the naming of the color of a group of Xs (XXXX) presented in red, green, and blue ink; and (3) Inhibition, on which subjects will be asked to identify the ink color of printed color names while disregarding the word itself (i.e., the word red printed in blue ink should be identified as blue). Both the WR and CN assess processing speed, while the inhibition task evaluates cognitive inhibition. Each task will be performed for a duration of 45 seconds, with subjects responding verbally as fast as possible. Any incorrect responses will result in interruptions, adding to the erroneous time and thus reducing the score. The raw score, denoting the number of correct responses within 45 seconds, will be compared against predicted values based on the individual’s age and educational level. The deviation between the actual and predicted scores will be calculated and then converted into age and education normative t-scores [38].

**Symbol Digit Modalities Test -Oral Version (SDMT)**: The SDMT-oral version is included as a supplementary measure of processing speed that does not have a motor component. It has been demonstrated to be sensitive to the presence of brain damage in numerous studies. The SDMT requires the subject to substitute a number for a randomized presentation of a geometric figure. The appropriate number is shown in a key containing the Arabic numbers 1–9, each with a different geometric figure [75]. As the examinee looks at each stimulus, they state the number that is paired with each symbol in the key. The SDMT will be administered over 90 seconds, with the number of correct responses recorded.

**California Verbal Learning Test-III (CVLT-III)**: The CVLT-III assesses verbal learning and memory. It consists of 16 words from 4 semantic categories presented orally over 5 trials and includes a 20-minute delayed recall trial and a recognition trial [76]. The normed score for each trial will be calculated based on participants’ ages and educational levels.

**Controlled Oral Word Association Task (COWAT)**: The COWAT is designed to provide a score representing verbal fluency. Participants are asked to generate and pronounce as many English words as possible beginning with each of the letters C, F, L (or F, A, S) for an alternate version post-exercise) in three serial trials or tasks lasting 1 minute each [77]. The score is calculated by summing the total number of correct words generated for each letter, across all three trials [78]. The total score represents the participant’s verbal fluency, with higher scores indicating better performance.

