## Methodology

### Study design

This is a case-control study that includes a group of individuals with SCI and a sex- and age-matched uninjured control group to examine the effects of injury on exercise responses. The study protocol includes one initial visit for consent and maximal exercise testing (Visit 1) and one experimental visit (Visit 2) during which participants are exposed to a single session of HIIE. Fig 1 illustrates the schedule of enrollment, assessment, and intervention for the study (Fig 1).

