Visit 2 will be scheduled two to seven days after Visit 1 to allow for recovery from the maximal exercise testing and to ensure that there is no significant change in physical activity levels between the visits. Participants will receive the same pre-visit instructions for both visits, including maintaining a consistent diet, which is important due to its impact on ANS function [54]. Similar to Visit 1, participants will empty their bladder upon arrival to limit reflex sympathetic activation. They will then be seated, and the TCD probes will be secured to measure CBFV. Cognitive function will be evaluated with standard neuropsychological measures including the California Verbal Learning Test-III (CVLT-III) [55], Symbol Digit Modalities Test-oral version (SDMT) [56], Color-Word Interference Stroop Test [57], and the Controlled Oral Word Association Test (COWAT) to assess learning and memory, processing speed, executive function, and verbal fluency, respectively. These domains have been shown to be impacted in people with SCI [58,59]. Following cognitive testing, participants will undergo baseline cardiovascular measurements, including 15 minutes of beat-to-beat BP and electrocardiogram (ECG) recording, followed by a 1-minute face-cooling test (FCT) [60,61] to activate parasympathetic nervous system, a 5-minute recovery and a 15-minute sit-up test (SUT) [62] to activate sympathetic nervous system. To ensure participant safety during these tests and the subsequent HIIE protocol, continuous beat-to-beat BP and ECG monitoring will be conducted. If resting systolic BP exceeds 220 mmHg, the session will be immediately terminated based on a conservative safety threshold, which is well below the established 300 mmHg emergency criterion in SCI [63]. In cases of low BP, continuous monitoring will be maintained, and safety decisions will be guided by symptom presentation, as no universally accepted hypotensive threshold exists for this population.

Participants will then begin with a 2-minute warm-up at 10% PPO, followed by a single bout of HIIE. The HIIE consists of three 20-second all-out efforts at 100% PPO, each separated by 120 seconds of active recovery at 10% PPO. After completing the HIIE, participants will perform a 3-minute cool-down at 10% PPO [64]. This 10-minute protocol is one-third the time commitment of current exercise guidelines for SCI [20], and is therefore feasible for the targeted population. Fig 2 illustrates the HIIE protocol (Fig 2).

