### Outcome measures

**Primary outcome measures**: The outcome measures for our primary objective will include HF HRV, LF SBPV, BRS, HR, and BP during supine assessments, FCT, and SUT, both pre- and post-a single bout of HIIE.

**Secondary outcome measures**: The outcome measures for our secondary objective will include CBFV during cognitive testing and cognitive performance assessed pre- and post-a single bout of HIIE.

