### Data analysis

To analyze the impact of HIIE on cardiovascular, cerebrovascular, and cognitive functions in individuals with SCI compared to controls, linear mixed-effects models (LMMs) will be utilized. These models will assess the main effects and interactions of group (SCI vs. controls) and time (pre-HIIE vs. post-HIIE) across different outcomes, with specific adjustments tailored to the type of function being analyzed. The general model can be structured as follows:

Y_ij_ = β_0 _+ b_i_ + β_1_Group_i_ + β_2_Time_j _+ β_3_Group_i _× Time_j _+ β4 × Covariates_i _+ ∊_ij_

Where:

Y_ij_ represents the dependent variable (e.g., HR, BP, HF HRV, LF SBPV, BRS) for subject *i* at time j (j = 0,1).Group_i_ is the SCI/control status for subject *i* (SCI: Group_i _= 1, Control: Group_i_ = 0).Time_j_ is the *jth* time point (pre-HIIE: Time_j_ = 0, post-HIIE: Time_j_ = 1).Covariates_i_ are additional covariate(s) for subject *i*. For dependent variables within cardiovascular and cerebrovascular functions: baseline physical activity levels. For cognitive function: pre-morbid intelligence and psychological distress.b_i_ is the random effect for subject *i* to account for within-subject correlation over time and is assumed independent N(0, σ_b_^2^).∊_ij_ is the residual error term assumed independent N(0, σ_∊_^2^).

Estimation of parameters will be analyzed by restricted maximum likelihood estimation (REML). Wald tests will be used to assess the significance of the predictors, with the significance level set at p < 0.05. All analyses will be conducted using RStudio (© 2009–2024 Posit Software, PBC).

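### The two COWAT forms share the letter F, and form and practice effects cannot be separated from the HIIE effect in within-group cognitive change

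*Protocol article*

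**What the plan says.** All places are in the protocol article.

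- **COWAT letters (Cognitive function).** Participants produce words "beginning with each of the letters C, F, L (or F, A, S) for an alternate version post-exercise". On scoring: "The score is calculated by summing the total number of correct words generated for each letter, across all three trials".
- **Alternate forms (Experimental procedure, paragraph after Fig 2).** "Alternate forms of the CVLT-III, SDMT, and COWAT will be used for post-HIIE assessments to avoid familiarization effects". The Stroop is not in this list, although the "Color-Word Interference Stroop Test" belongs to the battery described earlier in the same section.
- **Stroop (Cognitive function).** The scored quantity is given as "The raw score, denoting the number of correct responses within 45 seconds", then converted to age- and education-normed t-scores. Word order in the reading section is called randomized. A second version is neither described nor ruled out.
- **Outcome status (Outcome measures).** The secondary outcomes are "CBFV during cognitive testing and cognitive performance assessed pre- and post-a single bout of HIIE".
- **Design (Study design).** There is "one experimental visit (Visit 2) during which participants are exposed to a single session of HIIE". Both groups exercise, and no rest or sham retest is described.
- **Model (Data analysis).** Group, Time, Group x Time, subject-level covariates and a random subject intercept. There is no term for form or order.
- **Claims.** The Abstract (Results) hypothesizes better cognitive performance in the SCI group itself. The Discussion says that a post-HIIE response in the SCI group that resembles the controls' in direction and pattern may indicate benefit.

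**The concern.** There are two separate problems.

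The first is an internal contradiction. Alternate forms are used to prevent familiarization, yet the COWAT alternate reuses one of the three baseline letters on the same day.

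The second is attribution. If the second form is always the post-exercise form, a difference in form difficulty enters the pre-post change in full. So does the gain from having done the same kind of task earlier that day. Nothing in the design estimates either one without exercise.

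What is at stake is how the secondary cognitive results are read. A practice gain shared by both groups would look like improvement in the SCI group, and like a similar direction of change in both groups. Those are the two patterns that the Abstract and the Discussion treat as favourable.

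**Working it through.** The plan gives no figure on this point to reproduce. The check compares the text, works out which contrasts are affected, and adds an illustration under assumed effects.

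**1. Letter overlap.** Pre: {C, F, L}. Post: {F, A, S}. Intersection: {F}, which is 1 of 3 trials.

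**2. Which contrasts are affected.** For group g, let h be the HIIE effect, p the same-day practice effect and f the difference in form difficulty. The expected pre-post change is

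Δ_g = h_g + p_g + f_g.

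Under the article's coding (control = 0, SCI = 1; pre = 0, post = 1):

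- β2 = Δ_C = h_C + p_C + f_C
- β2 + β3 = Δ_SCI = h_SCI + p_SCI + f_SCI
- β3 = (h_SCI − h_C) + (p_SCI − p_C) + (f_SCI − f_C)

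The within-SCI change carries p and f in full. The interaction β3 carries them only to the extent that they differ between groups. The cognitive covariates (pre-morbid intelligence and psychological distress) are constant within a subject and enter without a Time interaction, so they cannot absorb either effect. Under a fixed order, a Form term could not be separated from Time.

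**3. What rescoring on non-shared letters would do.** The COWAT change is (A + S + F at post) − (C + L + F at pre). Dropping F leaves (A + S) − (C + L). The repeat gain on F disappears. F's own difficulty already cancelled, so the form difference (A + S) versus (C + L) stays as it was, now in a shorter and noisier score.

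**4. Illustration with assumed shifts.** Inputs: 15 per group and two-sided α = 0.05 (Sample size calculation). Assumptions: HIIE effect zero, and a combined form and practice shift of d SDs of the change score. The documents give no value for d. Rejection rates come from the noncentral t distribution, with noncentrality d√n for a pre-post test in n participants.

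| Assumed d | Within SCI, n = 15 | Both groups pooled, n = 30 |
|---|---|---|
| 0 | 5% | 5% |
| 0.2 | 11.2% | 18.5% |
| 0.3 | 19.2% | 35.5% |
| 0.5 | 43.8% | 75.4% |
| 0.8 | 82.1% | 98.8% |

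For example, d = 0.5 and n = 15 gives noncentrality 0.5 × √15 = 1.94. A 40,000-run simulation at d = 0.5 gave 44.2% within SCI.

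For Group x Time, an equal shift in both groups cancels (simulated rejection 4.9% at d = 0.5). If the shift differs between groups by δ SDs, noncentrality is δ√(15/2):

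| Assumed δ | Group x Time |
|---|---|
| 0 | 5% |
| 0.1 | 5.8% |
| 0.2 | 8.3% |
| 0.3 | 12.5% |
| 0.5 | 26.2% |

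**5. Counterbalancing from now on.** If m of n participants in a group had the fixed order and the rest are split evenly, the form bias left in the unadjusted mean change is f × m/n. With n = 15 this is f/3 for m = 5 and 2f/3 for m = 10. The article does not say how many have been tested. Practice is unaffected by counterbalancing.

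**The case against.** The strongest reply is that the planned analysis already compares groups. The models assess the "main effects and interactions of group (SCI vs. controls) and time (pre-HIIE vs. post-HIIE", the Abstract names the interaction, and the Discussion speaks of comparing changes between groups. Anything common to both groups drops out there. This stands. The interaction is not shown to be biased: the article says that these cognitive domains are affected in SCI, but a lower level of performance does not establish a different practice gain or form effect. The reply does not cover the within-SCI hypothesis or the reading of a similar direction of change.

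Three stronger readings are tempting, and the documents do not support them.

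- **That every post-test uses one fixed form.** This is explicit for the COWAT only. For the CVLT-III and SDMT it is the natural reading, but the article does not say which form comes first, and an alternate form could simply be the one not given at baseline.
- **That the Stroop is repeated unchanged.** This rests on its omission from the list of alternate forms. The text does not say that the item sequence is reused.
- **That a third of the COWAT total is repeated material.** F is one of three trials, but the score is a word count, so its share of the total is unknown.

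It can also be said that the forms may be equally difficult. Nothing in the documents shows otherwise, and nothing there establishes it. The shift sizes above are assumptions only.

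**Conclusion.** The point holds within limits. The shared letter is certain and contradicts the article's own reason for using alternate forms. Form and practice effects are also inseparable from HIIE in the within-group cognitive change, because no one is retested without exercise; for form, this assumes the natural reading of the order for the CVLT-III and SDMT. The Limitations section discusses fatigue as an influence on post-exercise cognition but does not mention practice or form.

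The size is unknown. Under assumed shifts of 0.2 to 0.8 SD of change, false rejection in the SCI group would run from about 11% to 82%. The Group x Time contrast keeps its 5% level unless the effects differ between groups. The outcomes are secondary and the primary cardiovascular analysis is not touched. The point should be acted on, but it does not threaten the trial.

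**What to change.** **Remaining participants**

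- Use COWAT letter sets with no shared letter.
- Counterbalance form order within each group for the CVLT-III, SDMT and COWAT, and include Form in the model.
- Use a different Stroop item sequence at retest, and say so.

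**Participants already tested**

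- Report C + L versus A + S as a sensitivity analysis only, stating that it removes the repeated F but not the difference in form difficulty.

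**All cognitive tests**

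- Base the HIIE conclusion on Group x Time. Because both groups exercise, this shows whether the change differs between SCI and controls; it does not measure the benefit within SCI.
- State, in Limitations and in the interpretation, that improvement within a group, or a similar direction of change in both, cannot be attributed to HIIE because practice is not controlled. Counterbalancing does not alter this.

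**Cost.** An order list; a COWAT letter set that changes part-way, so that Form needs a separate level for the replaced set; incomplete form balance overall, since recruitment began in February 2024; and a narrower within-group claim. The sample size does not change.

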### Equipment

**Data acquisition:** BIOPAC Systems, Inc. MP160 system will be used for data acquisition and analysis of physiological data. The MP160 is a 16-channel core system with a high-level transducer interface module that uses AcqKnowledge 5.0 software for visualization and processing. The specifications for each data modality are described below.

**Baroreflex sensitivity analysis:** BRS will be processed using transfer function analysis via MATLAB [79]. BRS is represented by the average gain between changes in systolic blood pressure and the R-R interval within the frequency range of 0.07–0.14 Hz, a range that is reliable for BRS assessment as it is not significantly influenced by respiratory rate [79]. The beat-to-beat BP data will be down-sampled to 250 Hz from 1000 Hz to align with the ECG dataset for this analysis [80].

**Cerebral blood flow velocity**: The Lucid M1 TCD system (NovaSignal, Los Angeles, CA), will be used to measure CBFV. The ultrasound probe will be secured over the temporal acoustic window using an adjustable headpiece to ensure stable and consistent signal acquisition. The sampling rate will be set at 1000 Hz.

**Electrocardiogram:** Bionomadix 3-lead ECG (DA100C, Biopac Systems, Goleta, CA) will be used to obtain the R-R interval. Electrodes will be attached after preparing the skin with an alcohol wipe to reduce impedance and improve signal quality. The sampling rate will be set at 250 Hz.

**Heart rate variability:** LabChart 8 Software with built-in heart rate variability (HRV) tools will be used for ECG clean-up, including a QRS detector, beat-to-beat analysis, and autocorrection for ectopic beats. High-frequency (HF; 0.15–0.45 Hz) HRV will be calculated from the spectral analysis of the R-R interval through LabChart 8 software [81]. Normalized HF HRV (HF HRV n.u.) will be calculated by dividing raw HF by (raw HF + raw LF HRV).

**Photoplethysmography:** ClearSight photo-plethysmograph (Edwards Lifescience Inc, Irvine, CA; formerly Nexfin BMEYE, Amsterdam, Netherlands), will be used on the index or middle finger to obtain blood pressure waveforms. As a quality control measure, calibration using the Physiocal™ vascular unloading algorithm will be used prior to each physiological test. The sampling rate will be set at 1000 Hz.

**Systolic blood pressure variability:** SBPV will be processed using the methods previously reported in MATLAB [44]. Occasional ectopic beats will be removed by substituting them with average values of the resting condition, and significant trends will be eliminated by subtracting the best-fit polynomial function. The low frequency (LF; 0.05–0.15 Hz) band will be identified using Fast Fourier Transform [44]. Subsequently, the absolute power of the LF SBPV will be calculated using power spectral density.

